In addition to a mass media approach, the health care setting can also be suitable for addressing parental smoking [30,31,32]. Winickoff and colleagues (2001) [33] found that 74% of smoking parents whose children are hospitalized would enroll in a free telephone counseling cessation program. Moreover, these parents are also more motivated to quit smoking, since they worry more about the consequences of their smoking for their children’s respiratory diseases [34]. In The Netherlands, youth health care could be an ideal setting to address parental smoking cessation, as the Dutch youth health care provides preventive health care to all children (aged 0 to 17 years old) [35]. In The Netherlands, all parents must visit youth health care centers 15 times in the first four years of their child’s life [35]. In addition, youth health care professionals are expected to address parental smoking (cessation) at least four times during that time, if applicable [36]. Research shows that it is considered to be the (youth) health care professional’s role to address parental smoking [37,38,39]. However, (youth) health care professionals experience several barriers in doing so (e.g., a lack of time, the possibility of damaging the doctor-patient relationship, and lack of confidence in own smoking cessation counseling skills) [38,39,40]. Therefore, it is essential to provide a convenient, user-friendly, and time-saving intervention to (youth) health care professionals that does not jeopardize the doctor-patient relationship. In the present study, a time-saving and convenient intervention will be provided that allows (youth) health care professionals to easily refer smoking parents to a telephone counseling (see the methods section for an elaborate description of our intervention).

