### 2.7. Sample Size

Based on the results of Schuck and colleagues (2014) [14], our power calculation (Stata 12.1, StataCorp., College Station, TX, USA) indicated that 72 parents per implementation approach (36 intervention and 36 control) is sufficient to detect 7-day prevalence abstinence at three months post-intervention with a large effect (*p*_1_ = 0.445, *p*_2_ = 0.121, Power = 0.80, α = 0.05). Because we want to examine differences in smoking cessation rates between the two implementation approaches, we have to double from 72 to 144 parents. Based on the drop-out rates at 3-month follow-up of Schuck et al., 2014 [14] (i.e., 10% in the control group and 3.9% in the intervention group), we will anticipate 10% drop-out. This means that we will aim to recruit a minimum of 158 participating parents in total.

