
### 2.10. Statistical Analyses

Statistical analyses will be carried out to assess whether the randomization results in an equal baseline distribution of relevant participant characteristics across conditions. In case of group differences at baseline, confounding variables will be included in subsequent analyses. All analyses will be conducted in accordance with the intention-to-treat principle (i.e., all parents randomized to one of the two conditions will be included in the analyses examining the study hypotheses) as per the Consolidated Standards of Reporting Trials [53]. Moreover, a completers-only analyses will be conducted, i.e., only parents with outcome data on all assessments will be included in the analyses. To compare cessation rates across different groups, logistic regression analyses will be conducted. In addition, Mplus will be used to test for moderation and subsequently, multi-group testing with bootstrapping will be conducted to assess differences between recruitment approaches. Effect sizes and 95% confidence intervals (CI) will be reported to determine the magnitude and effect of the intervention.

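### Cessation rates are to be compared between two non-randomised recruitment approaches, but the only covariate rule looks at the randomised arms, so differences in who enrols can pass for an approach effect

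*Protocol article*

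**What the plan says.** Section 2.4 randomises parents to telephone counselling or control only. Approach is the route by which a parent came in. Under 2.2, parents either respond to a school letter, an advertisement or a website, or are asked by a professional during a visit. Section 2.6 uses channel as a stratification factor, which balances the arms within each channel but does nothing to balance one approach against the other.

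Comparing approaches is a stated aim. Section 2.7 arrives at "72 parents per implementation approach (36 intervention and 36 control") and then doubles this to 144, giving the reason: "Because we want to examine differences in smoking cessation rates between the two implementation approaches".

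Section 2.10 plans logistic regression for cessation rates across groups and a test for moderation, after which "multi-group testing with bootstrapping will be conducted to assess differences between recruitment approaches". Its only covariate rule starts from analyses to "assess whether the randomization results in an equal baseline distribution of relevant participant characteristics across conditions", and confounders are added if groups differ at baseline. No check or covariate set is given for approach against approach.

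The Discussion (section 3) speaks of what the approaches do to (cost)effectiveness in causal terms. Section 4 says that a channel with low quit rates should not be used. Strengths and Limitations does not mention selection between approaches.

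**The concern.** Randomisation makes the arms comparable on average, so adjustment matters least there. The approaches have no such protection, and the plan has no rule for them. If parents entering by one route are more motivated, smoke less or are better educated, their quit rate will differ even when the route itself does nothing.

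The protocol gives reason to expect this. The Introduction says of parents whose children are hospitalised that "these parents are also more motivated to quit smoking", and both the Introduction and the Discussion favour health care partly because parents there are thought to be motivated. What is at stake is the implementation conclusion: a route could be credited, or a channel dropped, because of who enrolled through it, and the reader would not be told.

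**Working it through.** **The plan's own figure.** Inputs from 2.7: abstinence 0.445 and 0.121, with "Power = 0.80, α = 0.05". Sidedness is not stated; two-sided is assumed.

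- Mean rate: (0.445 + 0.121)/2 = 0.283.
- Uncorrected n per arm = [1.96·√(2·0.283·0.717) + 0.842·√(0.445·0.555 + 0.121·0.879)]² / 0.324² = 29.1, so 30.
- With continuity correction: 36 per arm, 72 per approach, 144 in all.
- 144 × 1.10 = 158.4, stated as 158.

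The figure reproduces and is not disputed. It is sized for counselling against brochure within one approach.

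**Precision of the direct comparison of approaches.** Assume 72 against 72 and 28.3% abstinence overall. The 95% half-width is 1.96·√(2·0.283·0.717/72) = 0.147, or 14.7 points.

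**Spurious difference with no approach effect.** Let a share f of parents be highly motivated, and let motivation multiply the odds of quitting. The shares and odds ratios are assumptions; the documents give none. The difference is (f₁ − f₂)·(p_high − p_low), with the overall rate held at 0.283.

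| Odds ratio | Shares | p_high, p_low | Spurious difference | Share of half-width |
|---|---|---|---|---|
| 2 | 60% v 40% | 0.352, 0.214 | 0.2 × 0.138 = 2.8 points | 19% |
| 4 | 80% v 40% | 0.382, 0.134 | 0.4 × 0.248 = 9.9 points | 67% |

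**A second model, keeping the two arm rates separate.** The odds ratio applies within each arm, and the rates equal 0.445 and 0.121 when half the parents are highly motivated. The approach again has no effect.

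| Odds ratio | Shares | Crude cessation | Crude OR | Chance of p < 0.05 | Ratio of treatment ORs |
|---|---|---|---|---|---|
| 2 | 60% v 40% | 29.5% v 27.1% | 1.13 | 6.2% | 1.00 |
| 3 | 70% v 40% | 32.0% v 26.4% | 1.31 | 11.5% | 1.02 |
| 3 | 75% v 35% | 33.0% v 25.5% | 1.44 | 16.8% | 1.03 |

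The last column separates the two comparisons. The direct comparison of cessation rates moves, and its false-positive rate rises above 5%. The arm-by-approach contrast, which the moderation and multi-group step examines, hardly moves, because treatment is randomised within each approach. It would move if the trait also changed how well counselling works.

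**Events available for adjustment.** Expected quitters: 0.283 × 144 = 40.8, about 41. Per approach this is about 20, of whom 0.121 × 36 = 4.4 are in the control arm.

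**The case against.** Four points can be made for the plan.

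- **The multi-group step compares randomised contrasts.** This stands. A reader might infer that moderation by approach is as confounded as the cessation comparison, or that the counselling effect itself is in doubt. The documents support neither: randomisation is stratified by channel, and a purely prognostic trait leaves the ratio of treatment odds ratios at 1.00 to 1.03. Nor would main-effect covariates remove differences in effect modifiers.
- **Whom a route attracts is part of its value.** This also stands in part. For choosing a route, the crude result is a legitimate quantity. Professionals also raise cessation before the study baseline, so baseline motivation may partly result from the approach, and adjusting for it could remove something of interest. The protocol does not say that this total result is its target, however, and it speaks of an effect.
- **The evidence on motivation is thin.** A reader might infer that the protocol shows health care entrants to be more motivated than mass media entrants. It does not. The sentence in the Introduction concerns parents of hospitalised children, parents who volunteer through media may be equally motivated, and eligibility (2.3) already requires an intention to quit. The size and even the direction of any imbalance are unknown.
- **An analysis plan that is not shown may name covariates.** It may, and the reference in 2.10 to group differences could be read more widely. But the preceding sentence ties the check to the outcome of randomisation, which cannot balance approaches. The article thus states a rule aimed at the arms beside a causal reading and a decision on quit rates.

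**Conclusion.** The point holds for the direct comparison of cessation rates between approaches. Followed as written, 2.10 leaves that comparison open to selection, while sections 3 and 4 interpret it causally and act on it. Under the assumed motivation differences the distortion is about 3 to 10 points against a 14.7-point half-width. The upper figure rests on a strong assumption (odds ratio 4, shares of 80% and 40%), so the range illustrates and does not predict.

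The primary randomised comparison is untouched, as is the counselling effect within each approach. The moderation result is sound as a description, but it cannot be credited to the approach itself if entrants differ in traits that modify the counselling effect. This is a worthwhile correction to a secondary aim, not a threat to the trial's main result.

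**What to change.** In 2.10:

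1. Tabulate baseline characteristics by approach as well as by arm.
2. For the comparison of cessation rates between approaches, report two estimates side by side: the crude one, described as the total result of a route including whom it attracts, and one adjusted for prespecified cigarettes per day, education and baseline motivation, whatever the balance between arms. Note that baseline motivation may partly result from the approach.
3. Describe both this comparison and the moderation result as observational associations among parents enrolled through each approach.

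Align sections 3 and 4 with this wording, including the statement on dropping a channel with low quit rates, and add selection between approaches to the limitations.

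The cost is wording and a few parameters. Cigarettes per day and education are stratification factors in 2.6, and motivation has to be measured at baseline to assess its increase (2.8). With about 41 quitters the set must stay small. Arm, approach and three single-parameter covariates make 5 terms, or 40.8/5 = 8.2 quitters per term. Three-level smoking and education would make 7 terms, or 5.8 per term. Continuous or ordered terms are therefore preferable, and the covariates should not be added to the multi-group model, where about 4 control-arm quitters per approach are expected.

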### 2.11. Process Evaluation

Our process evaluation will examine: (1) the recruitment success (i.e., the number of parents who signed up to be called by a smoking cessation coach divided by the number of parents who started the intervention) of the four implementation channels (i.e., primary schools, online mass media, general health care, and youth health care) as well as the overarching approaches (mass media and healthcare); (2) the number of the counseling phone calls parents received and whether this differs between the four implementation channels and overarching approaches; (3) the facilitators of and barriers to participation of parents and professionals in the implementation channels (e.g., whether the costs of the telephone counseling keep parents from receiving the counseling); and (4) parents’ experiences, opinions, and perceptions with regard to the telephone counseling (e.g., whether parents have suggestions for improvement of the counseling and whether there were any topics that were missing and should have been discussed during the sessions). In accordance with Linnan and Steckler (2002) [54] multiple important process evaluation components will be included, such as fidelity (e.g., whether health care professionals follow the recruitment protocol), reach (e.g., the extent to which parents were reached by the different implementation channels), and context (e.g., factors that affect the recruitment or telephone counseling). Questionnaires, semi-structured interviews, and focus groups will be used to collect the data at a process level.

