In sum, this effectiveness study takes a novel method by examining the recruitment success of two implementation approaches (i.e., a mass media approach and a health care approach) to test the (cost)effectiveness of a telephone smoking cessation counseling and whether the effectiveness depends on the implementation approach. The mass media approach includes two implementation channels: mass mailings through primary schools and online mass media. The health care approach also consists of two implementation channels: general health care and youth health care. A 2-arm RCT will be carried out to test the (cost)effectiveness of the telephone counseling. Based on earlier results of Schuck et al., 2014 [14], it is expected that parents who receive telephone counseling show higher smoking cessation rates at 3-month post-intervention compared to parents who receive the control condition. Concerning the implementation of the telephone counseling, a process evaluation of the recruitment success will be conducted for two implementation approaches. It is expected that (youth) health care will be a more promising implementation approach for connecting smoking parents with the telephone counseling compared to mass media channels (online approach and mass mailings trough primary schools), as most of these parents are motivated to quit and find it acceptable to be directed to telephone counseling in the context of their child’s health [11,34].

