#### 2.2.1. Mass Media Approach

##### Primary Schools

A random sampling strategy will be used to recruit smoking parents through their children’s primary schools across all 12 provinces of The Netherlands. The randomly selected primary school boards will be asked to (1) distribute invitation letters to all children (aged 4–12 years) and ask children to hand these letters to their parents or (2) send the letters directly to the parents via e-mail. The primary schools decide which option they prefer. The invitation letters, which are targeted on parents in general and not personalized, will include a description of the study’s purpose, frequency of the assessments, and inclusion criteria. Smoking parents recruited via primary schools will be able to register for the study by completing the registration form (active informed consent) on the study website or by returning the form via mail. After the completion of the registration form, the parents will be called by professional counselors of SineFuma (one of the Dutch certified quit lines). During this phone call conversation, parents will receive additional information about the study (e.g., parents who will be randomized to the telephone counseling might have to pay for the telephone counseling (based on the parents’ health insurance), whereas parents who are randomized to the control condition do not have to pay for their intervention) based on which they will either confirm or withdraw their registration.

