##### Online Mass Media

Parents will be recruited through social media and two smoking cessation websites, including the Dutch national smoking cessation website. With respect to social media, multiple paid Facebook advertisements will be created and used for several months. The advertisements will target on parents who are interested in smoking (cessation). Both format and message of the advertisements can differ, depending on what message and/or format will be more successful in recruiting parents who smoke. Whether advertisements are successful or not will be based on the click through ratio (i.e., the ratio of users who click on the Facebook ad of the total users who view the ad) and the costs per click on the ads. Parents who will be recruited through online mass media have to complete a short registration form (i.e., name, telephone number, and e-mail address) on the website of SineFuma so that they can be called by the coaches within one week. Parents who will fulfill the inclusion criteria will be given a description of the study. Parents who will not fulfill the inclusion criteria will not be included in the study, but they will be offered telephone counseling. Parents who will be willing to participate in this study will receive a registration form and will be asked to return the completed form (active informed consent) by mail or online on the study website.

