## 4. Conclusions

The results of this study will reveal whether the telephone counseling is effective in “real life” conditions. If the counseling will not be as strong as we expect we will search for reasons and try to clarify why our results do not correspond to the results of Schuck et al., 2014 [14]. Consequently, we will think about how the telephone counseling can be improved. The results of Hayes et al., 2017 [57] could be important and relevant suggestions for the improvement of the telephone counseling. This study will also provide information on how and where to implement the telephone counseling for smoking parents in the most optimal manner in The Netherlands. If all four implementation channels will turn out successful in recruiting smoking parents (i.e., high recruitment rates and similar costs/participant), we will be able to conclude that a combination of all four implementation channels should be used to implement the telephone counseling. In contrast, if only one implementation channel turns out to be unsuccessful (i.e., extremely low recruitment rates and/or low quit rates), this particular channel should not be used to implement this program.

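### Recruitment success is defined as sign-ups over starters, the inverse of a conversion rate, and the sign-up step differs between schools and the other channels

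*Protocol article*

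**What the plan says.** Section 2.11 (Process Evaluation) defines recruitment success as the number of parents who "signed up to be called by a smoking cessation coach divided by the number of parents who started the intervention". It is to be computed for each "of the four implementation channels (i.e., primary schools, online mass media, general health care, and youth health care) as well as the overarching approaches".

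Section 4 (Conclusions) says how recruitment results will be used. Channels count as successful with "high recruitment rates and similar costs/participant". A channel that turns out "unsuccessful (i.e., extremely low recruitment rates and/or low quit rates), this particular channel should not be used to implement this program".

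The hypothesis served by the measure is in the Introduction: "It is expected that (youth) health care will be a more promising implementation approach for connecting smoking parents with the telephone counseling", compared with the mass media channels.

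The entry routes are described in section 2.2:
- **Primary schools:** parents complete the study registration form, which carries the informed consent. "After the completion of the registration form, the parents will be called by professional counselors of SineFuma", and parents then confirm or withdraw.
- **Online mass media:** parents leave a name, telephone number and e-mail address and are called. The eligibility check and study description follow. "Parents who will be willing to participate in this study will receive a registration form", and returning it gives consent.
- **General and youth health care:** the professional registers the parent with permission. After that the process is the same as for online mass media.

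**The concern.** There are two separate problems.

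1. **Direction.** A measure named success should rise when a channel does better. Sign-ups divided by starters rises when a channel does worse. Section 2.11 does not say that a lower value is better, and section 4 uses high and low in the ordinary sense.
2. **Comparability.** The count of sign-ups is taken at different points of the recruitment path. In schools it is taken after parents have consented to the study. In the other three channels it is taken before they have been checked for eligibility or told about the study. Schools belong to the mass media approach, so the mismatch carries into the comparison of mass media with health care.

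At stake is the implementation aim. This ratio is the only explicit formula the article gives for recruitment success, and section 4 names recruitment rates among the grounds for keeping or dropping a channel.

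**Working it through.** The article gives no sign-up or starter counts and no value of the ratio, so there is no stated figure to reproduce. All counts below are assumptions chosen to show how the measure behaves.

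**Step 1: direction.** Let S be sign-ups and T starters. The written measure is S/T; a conversion proportion is T/S. If starters are a subset of sign-ups, S/T is at least 1. With S = 100:

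| Starters T | As written, S/T | Inverted, T/S |
|---|---|---|
| 80 | 1.25 | 0.80 |
| 40 | 2.5 | 0.40 |
| 10 | 10.0 | 0.10 |
| 0 | undefined | 0 |

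The order of the channels reverses between the two columns.

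**Step 2: entry step.** Assume 100 interested parents and 20 starters in every channel, so the channels truly perform alike. Online and health care count all 100 as sign-ups. Schools count only those who complete the consent form; take 30, 50 or 70.

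| School sign-ups counted | Schools S/T | Others S/T | Schools T/S | Others T/S |
|---|---|---|---|---|
| 30 | 1.5 | 5.0 | 0.67 | 0.20 |
| 50 | 2.5 | 5.0 | 0.40 | 0.20 |
| 70 | 3.5 | 5.0 | 0.29 | 0.20 |

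The gap comes from the definition alone, and inverting the ratio does not remove it.

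At the level of approaches, take the middle row:
- Mass media (schools plus online): T/S = (20 + 20)/(50 + 100) = 40/150 = 0.27.
- Health care (two channels): T/S = (20 + 20)/(100 + 100) = 40/200 = 0.20.

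The two approaches were set equal and appear different.

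**Step 3: what counts as starting.** Section 2.4 randomises parents to counselling or to the brochure, and section 2.2.1 calls what control parents receive an intervention as well. Section 2.7 plans equal arms (36 and 36 per approach). Section 2.4.1 reports that 87.5% of the counselling arm in the earlier efficacy trial received at least one call. With 100 sign-ups and 50 randomised equally:
- either arm counts: 100/50 = 2.0
- counselling arm only: 100/25 = 4.0
- counselling arm with at least one call: 100/(25 × 0.875) = 100/21.875 = 4.57

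The value more than doubles with the reading chosen. This factor is about the same in every channel, because section 2.6 stratifies randomisation by channel. It therefore affects the size of the measure and not the ranking, provided one definition is used throughout.

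**The case against.** The strongest reply is that the formula is a wording slip. Both counts are needed whichever way the ratio is written, so inverting it changes no data collection. Section 2.11 states no scoring direction, and a reader could take the ratio as sign-ups needed per starter, with lower being better. Section 4 speaks of recruitment rates and does not refer back to the formula. This stands in part: a reader might infer that the trial will rank its channels backwards, and the documents do not go that far. The reversal follows only if the written formula is used with the reading in section 4. But no other definition is offered and nothing says that lower is better, so the definition is wrong as it stands.

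On comparability, it can be said that the sign-up precedes the counsellor's call in every channel, and that a higher entry threshold is simply a feature of the school route. The first is true. It does not make a consented study registration equivalent to a contact form.

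Four stronger readings should not be drawn:
- **Reach and cost are ignored.** The ratio leaves them out, but section 2.11 lists reach as its own component, section 2.2.1 tracks click-through and cost per click, and section 2.9 monitors recruitment costs by channel and approach.
- **The brochure arm biases the channel comparison.** It does not; step 3 shows a common scaling.
- **Counselling outside the trial is confined to online and health care.** The general offer to ineligible parents is stated for the online route, which health care shares. But section 2.3 offers counselling to excluded pregnant women without limiting it to any channel. Nothing says that such parents count as starters.
- **The choice of channel rests on this ratio alone.** Section 4 also names cost per participant and quit rates.

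**Conclusion.** The point holds in two parts. As written, the measure is the reciprocal of conversion and conflicts with how section 4 reads recruitment rates. Separately, its sign-up count is taken at a different step in schools than elsewhere, so neither the written nor the inverted ratio compares like with like, between channels or between approaches.

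The direction error is a matter of definition and needs no numerical assumption. The size of the comparability problem depends on how many interested school parents do not complete the consent form, which the article does not give. Over the assumed range of 30 to 70 per 100, the inverted ratio for schools is 0.67 to 0.29, against 0.20 for equally performing channels.

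The consequence is limited to the implementation aim and the health care versus mass media hypothesis. The primary abstinence outcome and the sample size do not depend on this measure.

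**What to change.** 1. Swap the ratio in section 2.11: starters divided by sign-ups, with higher meaning better. Use the same term and direction in section 4.
2. State whether starting means counselling only or either randomised arm, and apply that in every channel. If it means counselling only, say that equal allocation caps the proportion at about one half of those randomised. Count parents counselled outside the trial separately.
3. For comparisons between channels and approaches, also report a proportion from a step that means the same everywhere: starters among parents who were eligible, consented and confirmed participation after the counsellor's call. Keep the sign-up-based proportion beside it, because it shows the losses before that step, and note that the school entry step is a consent form.

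Inverting the ratio alone is not enough, and neither is a denominator of parents registered or referred: that would still be a consent form in schools and a contact form or referral elsewhere.

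The cost is a wording change and a short tally at each step in each channel. Nothing new is needed for reach or for recruitment costs, which are already planned.
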